### Interpretive description

#### The interpretive description methodology

The qualitative component of the Hans Kai trial will follow an interpretive description design that will be implemented during and after the intervention by embedding a combination of convergent and explanatory sequential designs into the RCT. Interpretive description is a flexible qualitative research methodology for conducting rigorous qualitative research that generates knowledge relevant for clinical practice in the applied health disciplines [37, 38]. The overarching aim of interpretive description is to provide practical evidence on subjective experiences valuable in informing future decisions in health-related settings that impact the lives of different populations. In the context of the Hans Kai trial, this qualitative research methodology will be used to generate new knowledge on the subjective experiences of study participants whose findings are meaningful and applicable to clinical practice.

In this research, the interpretive description methodology will be used to investigate the experiences of Hans Kai program participants and facilitators to identify the main strengths and limitations of Hans Kai, uncover potential implementation issues, and elucidate the mechanisms through which the program works. This qualitative component of the trial will involve a multi-method approach in which multiple qualitative data collection methods will be used to reach a deeper and more nuanced understanding of the program strengths, how the program works, and for which people it is more effective in promoting health and wellbeing. Adaptable components of the program will also be investigated and modified according to the feedback provided by the trial participants.

#### Research objectives

##### The convergent component

The qualitative data that will be collected during the intervention component of the study will address process questions. This component of the study aims to (1) gain an understanding of the experiences of the program participants and facilitators with the program; (2) identify the strengths and weaknesses of the program, as well as the barriers and facilitators to implementing the program from the perspectives of the program participants and facilitators; and (3) receive feedback from program participants and facilitators to revise the modifiable aspects of the program. This data will complement the RCT outcome data.

##### The explanatory sequential component

Case-selection variant

The qualitative data that will be collected after the intervention component of the study will aid in interpreting the RCT outcome results and explaining why the intervention worked or did not work, or why it worked for certain participants but not others. Specifically, the aims of this qualitative strand are (1) to understand why the outcomes occurred; (2) to explain variations in outcome results across program participants; (3) to elucidate the mechanisms through which the program works; (4) to assess how context may influence the program effectiveness; and (5) to receive feedback from program participants and facilitators to revise the modifiable aspects of the program.

##### Participant selection

In keeping with the explanatory sequential research design—case-selection variant, to address the stated research objectives, three subsamples of program participants will be selected using purposeful sampling based on the results of the first outcome assessments (Time 2: 6-month follow-up). These three groups will include the following:*Group 1:* 8–10 program participants who experienced improvements of 25% or more in all or most outcomes measured between Time 1 (baseline) and Time 2 (6-month follow-up).*Group 2:* 8–10 program participants who between Time 1 and Time 2 experienced improvements of 25% or more in some outcomes *but* no change or any deterioration in other outcomes.*Group 3:* 8–10 program participants who experienced no change or any deterioration in all or most outcomes measured between Time 1 and Time 2.

Examining the perspectives of program participants who experience diverse program outcomes will aid in interpreting the results of the experimental RCT component by allowing to reach a deeper and richer understanding of the mechanisms through which the program works in promoting participants’ health and wellbeing, for whom, and under what circumstances.

#### Qualitative research activities

##### The convergent component

A short survey including a set of open-ended questions will be administered to all Hans Kai participants at Time 1a (at the termination of the health school) and Time 2 (6-month follow-up) to address the stated research objectives. The survey will include eight open-ended questions investigating what motivated study participants to join Hans Kai and what they hope to gain by participating in the program; their perceived strengths and weaknesses of the program; and the barriers and facilitators they experienced during the program. A similar survey including five open-ended questions will also be administered to all Hans Kai facilitators at the beginning of the RCT (Time 1: baseline).

##### The explanatory sequential component

Individual face-to-face in-depth semi-structured interviews will be conducted with a sample of 24–30 Hans Kai participants following the Time 2 outcome assessments (6-month follow-up) and then again at Time 3 (12-month follow-up or 1 year after participants enrolled in the program). The 24–30 participants will be purposefully selected based on the results of the Time 2 outcome assessments (see previous section for details) so that this subsample of study participants will include a combination of adults who experienced improvements, no changes, or deterioration in the health outcomes measured in the experimental component of the RCT to evaluate program effectiveness. The individual interviews will involve a set of open-ended questions that aim to investigate study participants’ subjective experiences in the Hans Kai program. Participants’ accounts generated through these interviews will aid in the interpretation of the RCT results. The same interview guide will also be used to conduct a focus group (involving 5–8 participants each) with all participants who will still be enrolled in Hans Kai 1 year after joining the program at Time 3. Additionally, at Time 1, 2, and 3 a purposefully selected sample of 30 program participants (10 at each timepoint) will be invited to participate in a photovoice project involving taking pictures regarding their subjective experiences of being and Hans Kai participant. Once the photovoice projects are complete, study participants will be invited to create a storytelling video describing their health journey before and during Hans Kai by integrating their pictures into a video. At Time 2 and Time 3, the photovoice participants will be selected using the same criterion used to select the individual interview participants to ensure including participants who experience diversified program outcomes.

#### Data analysis

All narrative and pictorial data collected during the qualitative research activities will be included in the qualitative analysis. Following recommendations by Charmaz [39, 40], in order to explore nuances of meaning and generate an understanding of study participants’ perspectives that accurately reflects their subjective experiences, two research team members will use a constant comparative method to analyze all qualitative data (narrative and pictorial). This method will entail engaging in both data collection and analysis simultaneously by conducting data collection and analysis in a parallel, iterative process, with coding of qualitative materials starting while the research activities are still in progress. This procedure will allow learning from the emerging data about participants’ subjective experiences since the beginning of the research process. This data will then be used to develop progressively more focused interview protocols.

Throughout the research process, informal analytic notes, commonly referred to as memos, will also be developed [39, 40]. Memo-writing represents a central tool in qualitative coding because it prompts us to analyze the data and codes early in the research process. To engage in memo-writing, we will stop and think about our participants, their experiences, and their meanings, as well as about our own experiences and preconceived assumptions through the process of reflexivity. We will write our memos for personal use in an informal language and in a spontaneous fashion, and we will create a “memo bank” to store our memos. Specifically, the interviewer will write extensive narrative descriptions that will include (i) fieldnotes about the data collection activities; (ii) memos about the data collection and analysis process; and (iii) reflexive notes about the interviewer’s personal assumptions [41]. In these personal, reflexive memos, which will be written at the conclusion of each interview, the interviewer will use reflexivity to acknowledge how their background, experiences, values, and beliefs may have impacted how the study was being conducted.

Transcribed interviews, group discussions, and survey responses, as well as photos and investigator memos, will be included in the analysis. In grounded theory, data analysis consists of studying the early data and begin to separate, sort, and synthesize these data through qualitative coding [39, 40]. Qualitative coding means naming segments of data with a label that simultaneously categorizes, summarizes, and accounts for each piece of data. Grounded theory coding requires us to stop and ask analytic questions of the data we have gathered to further our understanding of participants’ experiences of the Hans Kai program, and to help us direct subsequent data-gathering toward the analytic issues we are defining. In coding the qualitative materials, we will follow Charmaz’s recommendations to conduct coding in two main phases, including initial coding and focused coding, and by performing both an intra- and inter-participant thematic analysis [see 36 and 37 for more details].

#### Trustworthiness

In qualitative inquiry, trustworthiness of the data refers to the degree to which the study findings are supported by evidence and can be trusted as accurate reflections of participants’ perspectives on the research topic [42]. In the Hans Kai trial, the trustworthiness of the data will be ensured by implementing a series of strategies that endeavor the credibility, transferability, dependability, and confirmability of the data.

Credibility will be enhanced implementing methodological triangulation [42, 43]. Using multiple methodologies or data sources (including surveys, individual interviews, focus group discussions, and photovoice projects) to take a multifaceted view of study participants’ perspectives and subjective experiences will add rigor, depth, complexity, and richness to the research study. The findings of this qualitative component of the trial will provide essential context and meaning to the interpretation of the RCT results. Further strategies that will promote credibility involve using the qualitative data analysis software Nvivo for data management and analysis; confirming researcher understandings and interpretations of participants’ accounts by summarizing the main points of the individual interviews, photovoice projects, and focus group discussions to participants at the conclusion of each research activity; and engaging in extensive memo writing to support reflection on the emerging data and document procedures, insights, and analytic decision-making. Additionally, maximum variation sampling will be used to collect data from the widest range of perspectives possible and construct a holistic understanding of the factors that may impact the implementation and effectiveness of the Hans Kai program [44].

Transferability of findings to other contexts (settings and populations) will be endeavored through a “rich, thick description” of study participants and their multiple perspectives and subjective experiences that will help provide a clear description of the context in which the study findings were generated so that others will be able to determine whether the application of these findings to other populations is appropriate, given the characteristics of the two groups [42, 43]. Strategies used to increase the dependability of the qualitative findings will include continuity and trust in the relationship between the researchers and the study participants, and involvement of a researcher with qualitative research expertise who will assist in all steps of the research process and aid in ensuring that these conform to the standards necessary to provide an accurate representation of participants’ perspectives and experiences [43]. This researcher, together with other team members with content expertise, will also be involved in peer debriefing and audit trial.

Confirmability will be ensured by using participants’ direct quotes as evidence of the study findings [42]. Reflexivity will also be used throughout the research process to clarify investigator personal values, attitudes, assumptions, and worldviews that may impact the analytic decision-making process. In this regard, fieldnotes, memos, and reflexive notes will be used as part of the research team discussions to help the investigators take a reflexive stance by examining and clarifying how their past life experiences, worldviews, and assumptions may affect the research process [41]. Great attention will be paid to preventing these assumptions and biases from affecting the data analysis process.

### Integrating the quantitative and qualitative findings

In the final phase of the trial, the qualitative themes reflecting the unique experiences of the Hans Kai participants and facilitators will be used to explain the quantitative numeric RTC results on the effectiveness of Hans Kai by comparing the two sets of data. Specifically, after analyzing the quantitative and qualitative data, a joint display showing the relationship between the intervention benefits and participant experiences will be developed and used to integrate the two sets of data [22]. For each trial participant who completed at least one qualitative research activity, improvements, with magnitudes, as well as no changes and deteriorations, with magnitudes in all outcomes of interests will be listed in the joint display and connected to the themes reflecting each participant’s unique experience. Using the RCT outcomes, we will create typologies that illustrate different intervention benefits (e.g., benefits in physical health only, benefits in physical and mental health, or benefits in mental health only) and, for each category in the typology, we will interpret the RCT results by comparing the changes in the outcomes of interest with differing participant experiences. This will lead to additional insights into the effectiveness of the Hans Kai program. The qualitative themes reflecting facilitators’ experiences will be kept separate from the RCT results.

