The mixed methods RCT described in this protocol has been designed to address the methodological limitations of the previous study conducted to evaluate the Hans Kai program and provide evidence to clarify the mixed evidence regarding the effectiveness of peer-led health promotion programs. This clinical trial is innovative for several reasons. First, it is the first RCT to be conducted to evaluate the effectiveness of the Hans Kai program in the Canadian context, and therefore, it will either provide robust evidence on the effectiveness of this program in promoting the health and wellbeing of Canadian adults or clarify the reasons behind its ineffectiveness in this context. Additionally, the measurement of numerous wellbeing-related outcomes over time and the mixed methods nature of the trial make this a unique research study. During the clinical trial, numerous wellbeing-related outcomes will be measured to elucidate if the program is more effective in promoting certain areas of wellbeing rather than others. This information, together with the qualitative findings on program participants’ unique experiences in Hans Kai, will be useful in planning targeted enrolment of adults who are impacted by specific life circumstances or chronic conditions to optimize organizational resource use and positive outcomes in future Hans Kai participants. The extensive qualitative component of the trial will include program participants and facilitators and will help unveil the mechanisms through which Hans Kai works in promoting participants’ health and wellbeing. The integrated mixed method findings will help support the further development and use of Hans Kai as well as those of other peer-led health promotion programs in the Canadian context.

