#### Sample size

The primary analysis will be performed based on the pre- to post-intervention changes in the primary outcome, the Mental Health Continuum Short Form (MHC-SF) [23], comparing the mean change scores between the intervention and control participants, with a nested design to account for participant group membership in Hans Kai [24]. Based on data from previous studies [4, 24] and the RCT study design, we expect the changes from baseline MHC-SF scores within each subject group to be approximately normally distributed with a standard deviation of 5. The average within-group pre-post changes in MHC-SF scores in the Hans Kai prospective cohort study were + 6.5 in 34 participants at 6 months [18]. With a planned sample size that accounts for dropouts of 90 adults, with 60 intervention participants and 30 control participants, we would have a power of 80% to detect a true difference in the mean response of intervention and control participants of − 3.1 or 3.1 at the end of the 6-month RCT component [25]. This scenario assumes that the outcomes of each participant will be independent of the Hans Kai peer group they join. However, since part of the Hans Kai program includes forming groups, a very conservative power calculation considers the “effective” sample size for the Hans Kai program to be equal to the number of groups rather than the number of participants. We anticipate that 60 intervention participants will form 10 independent groups of six participants per group. In this very conservative scenario, with 10 groups in the intervention arm and 30 control participants, we would be able to detect a true difference in the mean scores of intervention and control participants of − 5.2 or 5.2 with 80% power. We believe that the actual study power will fall somewhere between the two scenarios presented here. With a starting sample size of 105 adults and an estimated 15% dropout rate during the study period [18], we expect to generate a minimum sample of approximately 90 participants at the 18-month follow-up.

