#### Statistical analysis

Preliminary analysis will involve computing descriptive statistics for all quantitative variables. For continuous variables, means, standard deviations, and quartiles will be estimated, while categorical variables will be summarized with counts and percentages in each category. Summaries will be performed by group and by assessment, as well as for the entire study group. Primary data analysis of the RCT portion will involve comparing the mean values of the within-subject changes in outcome variables from baseline to 6 months between the treatment and control groups. Secondary data analysis will include a test of the interaction between time in the Hans Kai program and the outcome measurements in all participants from 0 to 20 months. The primary analysis will be conducted at the 0.05 level of significance. In general, test results will be described as significant if their *p*-values are less than 0.05 without adjustments for multiple inference. Multiple imputation will be used to deal with missing data.

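### The integration step calls each Hans Kai participant's own before-after change an intervention benefit, with no control-arm benchmark for how often the same change occurs under standard care

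*Protocol article*

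**What the plan says.** The Statistical analysis section makes the trial's quantitative result a between-arm comparison of mean within-subject change from baseline to 6 months.

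The section on integrating the quantitative and qualitative findings works at the level of the individual. Everyone who completed at least one qualitative activity enters a joint display with their improvements, absence of change and deteriorations in every outcome, and these are linked to that person's themes. Then: "Using the RCT outcomes, we will create typologies that illustrate different intervention benefits". The examples are benefit in physical health only, in mental health only, or in both. The section expects this to add to what is known about the programme's effectiveness. It gives no cut-off for a benefit and no role to the control arm.

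Under Qualitative research activities, the participant surveys, interviews, focus groups and photovoice are all for Hans Kai participants. Participant selection picks interviewees from programme participants by their own change to 6 months, using an improvement of 25% or more.

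The stated uses are explanatory. The explanatory sequential component is meant to help in "explaining why the intervention worked or did not work, or why it worked for certain participants but not others". The Background says that the outcome information, together with the qualitative findings, "will be useful in planning targeted enrolment of adults who are impacted by specific life circumstances or chronic conditions".

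**The concern.** One person's change from baseline to 6 months is not that person's programme effect. It mixes any effect with measurement error, regression to the mean and ordinary fluctuation. Entry also requires self-reported motivation to change lifestyle (Participants), so some improvement under standard care is plausible.

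The randomised control arm exists to separate these components, and this step does not use it. The Background itself counts the correlational design of the earlier pre-post evaluation among its limitations and says this trial was designed to address them. The integration step brings uncontrolled before-after attribution back in.

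At stake is what the trial may say about why and for whom Hans Kai works. If types of benefit fill up partly by chance, themes will be matched partly to noise.

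**Working it through.** **Inputs**
- SD of individual MHC-SF change: "approximately normally distributed with a standard deviation of 5" (Sample size).
- Numbers analysed: "with 60 intervention participants and 30 control participants" (Sample size).
- Level: "The primary analysis will be conducted at the 0.05 level of significance" (Statistical analysis). Two-sided testing is inferred, because the detectable difference is given with both signs.
- Power: "we would have a power of 80% to detect a true difference in the mean response of intervention and control participants" of 3.1 in either direction (Sample size).
- Assumption for this illustration: any change above zero counts as a benefit.

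**1. The plan's own figures.** Detectable difference = (1.960 + 0.842) × SD × √(1/n₁ + 1/n₂).
- 60 versus 30: 2.802 × 5 × √(1/60 + 1/30) = 3.13 (3.17 with the noncentral t). The protocol states 3.1.
- The conservative scenario, "with 10 groups in the intervention arm and 30 control participants": 2.802 × 5 × √(1/10 + 1/30) = 5.11 (5.25 with the noncentral t). The protocol states 5.2.

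Both reproduce, so the SD of 5 is the value the protocol worked with. The concern does not depend on the sample size; the SD serves only to size individual variation.

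**2. No programme effect and no drift.** Individual change ~ Normal(0, 5).
- P(change > 0) = 1 − Φ(0) = 50%, about 30 of 60.
- P(change ≥ 5) = 1 − Φ(5/5) = 16%.
- Middle 80% of changes: ±1.2816 × 5 = −6.4 to +6.4.

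**3. The same true gain of 3.1 for everyone.** Individual change ~ Normal(3.1, 5). By construction nobody responds better than anybody else.
- P(change < 0) = Φ(−3.1/5) = Φ(−0.62) = 27%, about 16 of 60.
- P(change ≥ 5) = 1 − Φ((5 − 3.1)/5) = 1 − Φ(0.38) = 35%, about 21 of 60.

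The display would show apparent gainers and decliners to explain, and the difference between them would be entirely noise.

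**4. How far a stricter cut-off helps.** Suppose the 25% from Participant selection were used for the typology. The null probability of a gain that large is 1 − Φ(0.25 × baseline / 5). The article does not give the baseline MHC-SF score, so a range is assumed.

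| Assumed baseline | 25% of baseline | P(gain ≥ 25%), no effect |
|---|---|---|
| 20 | 5.0 | 15.9% |
| 30 | 7.5 | 6.7% |
| 40 | 10.0 | 2.3% |
| 50 | 12.5 | 0.6% |

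The false-label rate on the MHC-SF therefore runs from 50% at a zero cut-off to under 1% at a 25% cut-off with a high baseline. The integration section does not say which rule applies.

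**The case against.** The strongest reply is that this is a secondary, interpretive strand. The effectiveness claim comes from the between-arm analysis, which will be known when the display is built. No change and deterioration are listed as well, and the plan asks why the programme did not work as readily as why it did. Participants' own accounts are evidence beyond a change score. The article is condensed, so typology rules and caveats may stand in the full protocol.

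Much of this stands. The primary comparison is untouched, the plan does not presuppose success, and an unstated cut-off alone would be no finding. But the label and the inference to effectiveness are written out, and further detail would not make the label accurate. Listing deteriorations does not show how often the same profiles arise under standard care.

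Three stronger readings are tempting and not supported:
- A reader might infer that most interviewees would be labelled as benefiting by chance. Interviewees are filled by quota on outcome: 8–10 improvers, 8–10 mixed, and 8–10 with no change or deterioration in all or most outcomes. Chance rates for unselected participants do not describe them.
- A reader might infer that targeted enrolment rests on this display. The Background bases it on the measured outcomes together with the qualitative findings in general; the display is one contributor.
- A reader might take the 50% as a forecast. It holds only for a zero cut-off, no programme effect and no average drift.

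**Conclusion.** The concern holds, confined to the integration step. As written, that step attributes uncontrolled individual change to the programme and draws on it for insight into effectiveness. It contributes to the why and for-whom conclusions and to planning targeted enrolment, but is not their only basis.

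For unselected programme participants and a zero cut-off, 50% would show some MHC-SF improvement with no effect, and about 27% would appear to deteriorate even if everyone truly gained 3.1. These figures rest on the protocol's SD of 5, on normality, and on all variation around the mean being unrelated to the programme. A stricter cut-off lowers the false-label rate by an amount that cannot be fixed without the baseline score. It also cannot replace the control arm as a benchmark, because it does not show how many controls pass the same threshold.

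**What to change.** In the section on integrating the quantitative and qualitative findings:

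1. Rename the types *changes observed during the programme*.
2. State the cut-off. Apply the same typology rules to all programme participants and all control participants with 6-month RCT data, and show both sets of proportions in the joint display. The programme proportion must not be taken over the quota-selected interviewees or only those in qualitative activities, because the comparison with controls would then be invalid.
3. Note beside the display that the section on the 6-month RCT times the arms differently: the programme arm's full assessment falls 6 months after the 2-month health school (about 2 + 6 = 8 months after it begins), the controls' 6 months after enrolment.
4. Reserve *intervention benefit* and for-whom statements for what the randomised comparison supports. Treat the rest as hypothesis-generating.

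Controls already complete the full assessments at baseline and 6 months (Procedure; The 6-month RCT), so no new participants, visits or interviews are needed. The cost is a little extra analysis and more cautious qualitative conclusions.
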